### **Data collection**

Demographic data will include:

- Age
- Gender
- Ethnicity
- Race
- If the participant holds a healthcare card

Medical history will include (to the extent that details are known):

- Date of diabetes diagnosis
- Diabetes type

- History of peripheral artery disease and related conditions
- Details of peripheral neuropathy
- Date of ulcer onset
- Details of previous ulcer assessments
- Details of previous interventions/treatments relevant to DFU
- History of cardiovascular events
- History of renal disease with or without dialysis
- Use of immunosuppression
- Smoking status current / past

| Study period        | Screening | Treatment and Evaluation |                  |                  |                  |                  |                  |                                 |                  |                  |                     |
|---------------------|-----------|--------------------------|------------------|------------------|------------------|------------------|------------------|---------------------------------|------------------|------------------|---------------------|
| Visit number        |           | 1                        | 2                | 3                | 4                | 5                | 6                | 7                               | 8                | 9                | 10                  |
| Study Week          |           | 1
(weekly)            | 2                | 3                | 4                | 5                | 6                | 8
(Fortnightly
follow-up) | 10               | 12               | 18
(Final visit) |
| Study treatment     |           | X                        | X                | X                | X                | X                | X                |                                 |                  |                  |                     |
| Study day           |           | 0                        | 7                | 14               | 28               | 35               | 42               | 56                              | 70               | 84               | 168                 |
| Window days         |           | +/- 3                    | +/- 3            | +/- 3            | +/- 3            | +/- 3            | +/- 3            | +/- 7                           | +/- 7            | +/- 7            | +/- 7               |
| Informed consent    | X         |                          |                  |                  |                  |                  |                  |                                 |                  |                  |                     |
| Eligibility review  | X         | X                        |                  |                  |                  |                  |                  |                                 |                  |                  |                     |
| Demographics        | X         |                          |                  |                  |                  |                  |                  |                                 |                  |                  |                     |
| Medical history     | X         |                          |                  |                  |                  |                  |                  |                                 |                  |                  |                     |
| Physical assessment | X         | Symptom-directed         | Symptom-directed | Symptom-directed | Symptom-directed | Symptom-directed | Symptom-directed | Symptom-directed                | Symptom-directed | Symptom-directed | Symptom-directed    |
| Vital signs         | X         | X                        | X                | X                | X                | X                | X                | X                               | X                | X                | X                   |

Any medications or dressings/ulcer treatments used by participants in the 21 days prior to Day 0 and or/during the study will be documented in the participant notes. This record should include the treatment name, the dose and frequency, form and route of administration, the start and stop date of administration, and the indication for which the treatment is being used.

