**2 STUDY OBJECTIVES AND OUTCOME MEASURES**

**Table 1 Study Objectives and Endpoints**

| Primary Objectives                                                                        | Primary Outcome Measures                                                                                                                                                                                                                                              |
|-------------------------------------------------------------------------------------------|-----------------------------------------------------------------------------------------------------------------------------------------------------------------------------------------------------------------------------------------------------------------------|
| To assess the safety and tolerability of PAW up to 6 weeks after initiation of treatment. | The primary safety analysis will be performed based on data collected up to 6 weeks after initiation of treatment. Assessment of safety will be based on the Incidence and severity of adverse reactions, including but not limited to skin irritation or maceration. |

| Secondary Objectives                                                              | Secondary Outcome Measures                                                                                                                                                                                                                                                                                                                                                                                                                                                         |
|-----------------------------------------------------------------------------------|------------------------------------------------------------------------------------------------------------------------------------------------------------------------------------------------------------------------------------------------------------------------------------------------------------------------------------------------------------------------------------------------------------------------------------------------------------------------------------|

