| To evaluate the efficacy of PAW, at 12 and 18 weeks after initiation of treatment | 
Efficacy analysis will be performed based on data collected up to 18 weeks after initiation of treatment. Assessment of efficacy will be based on the following outcome measures of the study ulcer:
 
 
• Days to complete ulcer healing
 
• Presence and severity of infection
 
• Changes in wound quality based on ulcer assessment
 
• Quality of Life (Cardiff Wound Impact Schedule)
 
 |

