1. PAW
2. Control (sterile saline)

Participants will receive the appropriate rinse, applied to gauze as a temporary dressing, for ten minutes during a clinic appointment.

**Design:** A randomised, controlled, prospective trial. Participants will be patients with DFU.

**Blinding:** All clinical personnel and all participants will be blind to the assignment and treatment administered (double-blind). Only [name] will retain knowledge of treatment based on preparation of treatment and linkage on a spreadsheet with study ID. This spreadsheet will be used to match for study safety and efficacy on end of study, and/or once an SUSAR has been confirmed.

**Screening and Randomisation:** Participants who provide consent to participate in the study and meet all eligibility criteria and no exclusion criteria will be randomly assigned to one of the two groups.

**Treatment and Evaluation Period:** Participants will attend a total of 12 scheduled visits over 6 weeks, plus follow-up wound review visits fortnightly until week 12 and final visit at week 18.

A study flow diagram is provided in Figure 1.

[figure not shown]

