### Study Period/Duration of Participation

The study will involve:

- A treatment (six weeks) with follow-up for six weeks (fortnightly) and at six weeks following.

Total: approximately 18 weeks per participant.

The overall study period is expected to be September 2025 to August 2026.

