## **Withdrawal of Participants from Study**

Participants can terminate their study participation at any time and without giving a reason, without prejudice to further treatment. Participants who discontinue from the study will be asked about the reason(s) for their discontinuation only to determine the presence of any AEs. If possible and willing, they will be seen and assessed by an Investigator and have a final study visit. AEs should be followed up until resolved or stable and determined to be chronic.

Participants who withdraw from the study prior to the final scheduled visit will have the final visit procedures conducted at the time of withdrawal, if possible. If a participant withdraws due to the need for amputation of the foot/limb with the study ulcer, they will be asked to have the final visit procedures prior to the amputation, if possible.

If a participant withdraws due to the study wound being completely healed, they should have the final visit procedures.

On withdrawal, participants will have the opportunity to request that their existing data and samples be expunged from the study, to the extent it is possible to do so.

The Principal Investigator can exclude a participant from continuing in the study. Possible reasons for discontinuing a participant may include:

- Participant withdrawal of consent
- Inability to tolerate the study treatment
- Any unacceptable AEs, in the judgement of the Principal Investigator
- Participant's non-adherence to the protocol
- The use of another investigational research agent prior to Week 6 has been deemed necessary
- Termination of the study for administrative, financial, or other reasons.

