### **Overview of Study Visits**

Study procedures should be performed at relevant study visits in accordance with the schedule of procedures outlined in Table 1. The Principal Investigator or other study doctor will be present for study treatment at screening and at the week two visit at minimum to ensure patient safety and observe for AEs.

Participants will only be enrolled and randomised to study treatment if they meet all eligibility criteria, and none of the exclusion criteria.

Study visits will be arranged at Royal Adelaide Hospital and/or The Queen Elizabeth Hospital, aligning with patient clinical visit scheduling where possible to minimise inconvenience to participants. A window of plus or minus three days is permitted for Visits 1 to 6, and a window of plus or minus seven days is permitted for follow-up Visits 7-10. Study visits via home visit are permitted for Visits 3-10.

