## **6 EFFICACY ASSESSMENT**

### **Ulcer Healing Assessments**

The Investigator/nurse will inspect the study ulcer at each site visit for physical (rate of healing) characteristics.

An ulcer will be considered completely healed if there is 100% reepithelialisation of the ulcer surface with no trace of exudate or drainage, as determined by the Investigator. The date of complete healing will be recorded as the date of the first assessment of 100% reepithelialization.

Note: if a participant withdraws from the study because their study wound is completely healed, they should complete Week 24 assessments.

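### The schedule's Study day row puts the Week 18 final visit on Day 168 (Week 24) instead of Day 126, and skips Day 21 in a treatment block headed weekly

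*Protocol*

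**What the plan says.** The schedule of procedures gives each visit a study week, a study day and a window.

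- **Visit 10:** week label "18 (Final visit", Study day 168, window 7 days either side.
- **Visits 7 to 9:** Weeks 8, 10 and 12 on Days 56, 70 and 84.
- **Visits 1 to 6:** Weeks 1 to 6, headed weekly, on Days 0, 7, 14, 28, 35 and 42. The Overview of Study Visits adds: "A window of plus or minus three days is permitted for Visits 1 to 6".

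Elsewhere the protocol sets the timing as follows.

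- **Overall Study Design:** "plus follow-up wound review visits fortnightly until week 12 and final visit at week 18".
- **Study Period/Duration of Participation:** "A treatment (six weeks) with follow-up for six weeks (fortnightly) and at six weeks following", with a stated total of about 18 weeks per participant.
- **Table 1, secondary outcomes:** "Efficacy analysis will be performed based on data collected up to 18 weeks after initiation of treatment".
- **Table 1, primary outcome:** "The primary safety analysis will be performed based on data collected up to 6 weeks after initiation of treatment".
- **Ulcer Healing Assessments (section 6), for a participant who leaves because the ulcer has healed:** "they should complete Week 24 assessments".
- **Withdrawal of Participants (section 3), same situation:** "If a participant withdraws due to the study wound being completely healed, they should have the final visit procedures".

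**The concern.** Visit 10's week and day cells name times six weeks apart, and the treatment days do not match their weekly heading.

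The row is operative. The Overview of Study Visits tells staff to follow the schedule. Criteria for Postponing or Stopping Study Treatment lets a deferred application go ahead only if the visit can still fall inside its window. The day cells therefore decide when visits are booked and whether a postponed dose may be given.

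A site that booked by the day row would hold the last visit six weeks late. That is past the stated length of participation and past the 18-week efficacy horizon in Table 1. Adverse event collection, which runs until a participant completes or withdraws, would lengthen by the same amount. An ulcer still open at Visit 9 would have its next scheduled study assessment 84 days later instead of 42.

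In the treatment block, one dosing interval is twice the stated one. The last application also sits on the boundary of the primary safety period in a first-in-human study.

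**Working it through.** Inputs are the week, day and window rows of the schedule, and the 18-week and 6-week statements listed above. Day 0 is taken as the first application. Two week-to-day rules were tried: day = 7 × week, and day = 7 × (week − 1).

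| Visit | Week | Day in plan | 7 × week | 7 × (week − 1) | Days since previous visit |
|---|---|---|---|---|---|
| 1 | 1 | 0 | 7 | 0 | – |
| 2 | 2 | 7 | 14 | 7 | 7 |
| 3 | 3 | 14 | 21 | 14 | 7 |
| 4 | 4 | 28 | 28 | 21 | 14 |
| 5 | 5 | 35 | 35 | 28 | 7 |
| 6 | 6 | 42 | 42 | 35 | 7 |
| 7 | 8 | 56 | 56 | 49 | 14 |
| 8 | 10 | 70 | 70 | 63 | 14 |
| 9 | 12 | 84 | 84 | 77 | 14 |
| 10 | 18 | 168 | 126 | 119 | 84 |

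The second rule fits Visits 1 to 3 only and the first fits Visits 4 to 9 only. Neither gives Day 168 for Week 18.

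**Final visit**
- The plan's figure: 168/7 = 24 weeks.
- From the 18-week statements: 18 × 7 = Day 126.
- From Visit 9 plus six weeks: 84 + 42 = Day 126.
- Error: 168 − 126 = 42 days.
- Windows: 168 ± 7 is Days 161–175, and 126 ± 7 is Days 119–133. They are 161 − 133 = 28 days apart.
- Counting from Week 1 = Day 0 gives Day 119. That lies inside 126 ± 7, so the choice of rule does not rescue 168.

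**Treatment block**
- The intervals are 7, 7, 14, 7 and 7 days. The long one lies between Visits 3 and 4 only.
- Visit 3 is Days 11–17 (14 ± 3) and Visit 4 is Days 25–31 (28 ± 3).
- The shortest compliant interval is 25 − 17 = 8 days and the longest is 31 − 11 = 20 days. No compliant pair is 7 days apart.

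**Sixth application against the primary safety cutoff (6 × 7 = Day 42)**
- As scheduled: Day 42 ± 3 is Days 39–45. The time left before the cutoff runs from 42 − 39 = 3 days to 42 − 45 = −3 days, and is 0 at the nominal day.
- If Visit 6 were on Day 35: Days 32–38, which leaves 42 − 38 = 4 to 42 − 32 = 10 days, and 7 at the nominal day.
- Cost of that move: Visit 6 to Visit 7 becomes 56 − 35 = 21 days, where the present 56 − 42 = 14 days agrees with fortnightly follow-up.

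**The case against.** The arithmetic is not open to dispute, and the row is not a reading artefact: all ten day cells are present and line up with the visits and windows. The objections concern how much follows from it.

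- **A late final visit is not certain.** The same column says Week 18 and other sections repeat it, so a site may query the cell before booking Day 168. This stands: the consequence is conditional on following the day row.
- **A reader might infer that reactions to the sixth application would be lost.** The documents do not support that. Recording of Adverse Events covers consent to completion or withdrawal, and Safety Data tabulates treatment-emergent events by treatment with no Day 42 limit. What is affected is whether such reactions count in the six-week primary safety data.
- **A reader might infer a biased time-to-healing or censoring analysis.** No censoring rule is stated. Healing is dated by the assessment at which it is first seen, and Efficacy Analyses plans descriptive summaries only. That section also stops at 12 weeks, which would exclude Visit 10 on either day. Only Table 1's 18-week horizon makes the visit's day matter for efficacy.
- **The repair of the treatment days is not dictated by the text.** Visits 1 to 3 follow one rule and Visits 4 to 6 another, and nothing shows which group is misnumbered. Moving Visit 6 to Day 35 would create a 21-day interval where follow-up is described as fortnightly. This stands, so the choice is the sponsor's.

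**Conclusion.** The Study day row is wrong in two places and should be corrected.

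1. **Visit 10.** Day 168 should be Day 126. The error is 42 days, against a window of 7 days either side. Week 24 in the healing section is the matching slip for what the withdrawal section simply calls the final visit. One could guess that both come from a 24-week design, but the documents do not say so.
2. **Visits 1 to 6.** The row skips Day 21. This leaves 14 days between Visits 3 and 4 (8 to 20 within the windows) under a weekly heading. It also puts the sixth application on the nominal primary safety cutoff, or up to 3 days after it within the window. Reactions to that dose may fall outside the primary safety data while still appearing in the adverse event tables.

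The conclusion assumes that Day 0 is the first application and that the repeated 18-week statements express the intent. The consequences are for visit booking, the dosing interval and the boundary of the primary safety data. No test, power figure or sample size changes, since efficacy is descriptive and no formal sample size was calculated. The Overall Study Design's count of 12 visits over 6 weeks is a separate mismatch that this row does not settle.

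**What to change.** **Final visit.** Change Day 168 to Day 126 (window Days 119–133). In Ulcer Healing Assessments, replace the Week 24 reference with the final visit (Week 18) procedures, in line with the withdrawal section. This costs one cell and one sentence.

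**Treatment days.** The sponsor should choose one schedule and make the row match.

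- **Option (a), weekly dosing:** Days 0, 7, 14, 21, 28 and 35. Accept or adjust the resulting 21-day interval to Visit 7, and state that adverse events are collected by onset date up to Day 42. This leaves 4 to 10 days of observation after the last application before the cutoff. It costs three cells (Visits 4 to 6), a footnote on how weeks map to days, and one sentence on adverse events.
- **Option (b), Visit 6 stays on Day 42:** state the 14-day interval between Visits 3 and 4 explicitly. Then either cap the Visit 6 window at Day 42 or extend the primary safety cutoff past the last application. The cap only prevents dosing after the cutoff, leaving 0 to 3 days of observation. Extending the cutoff is what brings reactions to the sixth dose into the primary data. It costs a note on the interval plus a change to the Visit 6 window or to the primary outcome wording in Table 1.

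Either option is a short protocol amendment with no effect on the number of participants.

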### **Identification of the Study Ulcer**

If the participant has two or more diabetes-related foot ulcers that meet the eligibility criteria, only one will be selected as the 'study ulcer' (i.e., the ulcer that will be treated with study treatment and used as the basis of outcome measures). The ulcer selected should be the one with the largest area. Other ulcers will be treated by standard of care throughout the study.

The location of the study ulcer will be recorded as the foot (left or right), surface (plantar, dorsal, medial, or lateral), and area (forefoot, midfoot, hindfoot). Toe locations will be recorded from first (hallux) to fifth (the outermost toe).

### **Safety and Tolerability Assessments**

Safety will be assessed by physical examinations, vital signs, laboratory tests, wound characteristics and recording of AEs.

#### **Physical Examinations**

Physical examinations will include:

- Height (at screening only).
- Weight.
- A symptom-directed physical examination, including thorough assessment of the index ulcer and leg.
- ABI and toe pressure (screening only).
- New or worsening clinically significant abnormalities will be reported as an AE.

#### **Vital Signs**

Prior to first study treatment, vital signs will be measured after the participant has been sitting or supine for five minutes and will include pressure on both arms, pulse rate, respiratory rate and body temperature.

#### **Laboratory Tests**

Blood samples will be taken twice throughout the course of the study for safety assessments – at screening and at two weeks - plus as clinically indicated. These are part of routine clinical care in this cohort. The following specific tests will be performed:

- Haematology: Haemoglobin, haematocrit, red blood cell (RBC) count, white blood cell (WBC) count with differential, and platelet count.

- Clinical chemistry: Sodium, potassium, calcium, serum albumin, total protein, gamma glutamyl transferase (GGT), aspartate aminotransferase (AST), alanine aminotransferase (ALT), alkaline phosphatase (ALP), total bilirubin, lactate dehydrogenase (LDH), glucose and creatinine. Creatinine clearance is calculated based on Cockcroft-Gault equation, not raw serum creatinine.
- HbA1c will be performed at Screening (unless recent result is available).

### **Wound characteristics assessments**

At each study visit, a clinical Investigator will assess the characteristics of the study ulcer using the Monash Wound Assessment used throughout our clinical practice:

- Location
- Type – neuropathic, ischaemic, neuro-ischaemic
- Size - length, width, depth (post debridement).
- Involvement of deep structures, sinus tracts, tunnelling
- Wound bed tissue type
- Signs of infection
- Exudate - type and quantity
- Odour
- Pain

## **5 ADVERSE EVENTS**

Participants will be questioned and monitored throughout the study with regard to any adverse events (AEs) they may have experienced. An AE can therefore be any unfavourable and unintended sign (including an abnormal laboratory finding), symptom, or disease temporally associated with the use of a medicinal product, regardless of relationship to the medicinal (investigational) product.

Determinations of severity and causality of any AE can only be determined by a clinical Investigator without awareness of whether the treatment used is PAW or control.

An AE shall be classified as serious (a Serious Adverse Event, or SAE) if, in the opinion of either the Investigator or the Sponsor, it:

- Results in death.
- Is life-threatening, i.e., in which the participant was at risk of death at the time of the event.
- Results in permanent impairment of a body structure or body function
- Requires in-patient hospitalisation or prolongation of existing hospitalisation.
- Results in persistent or significant disability/incapacity.

Important medical events that are not immediately life-threatening and that do not result in death or hospitalisation may still be considered serious if, in the opinion of the Investigator, they jeopardise the participant or require intervention to prevent one of the other outcomes listed above. Such events should also be treated as SAEs.

